## Abstract

**Background:**

GHB dependence is a growing health problem in several western countries, especially the Netherlands. Attempts to stop using GHB are often followed by relapse shortly after successful detoxification. Craving for GHB use and co-morbid psychiatric symptom levels are thought to be the major factors contributing to the high relapse rates. Given its pharmacological profile, baclofen might prove an effective anti-craving agent for patients with GHB dependence. The aim of the current study is to assess the potential of baclofen as an anti-craving agent relapse prevention intervention in GHB dependent patients.

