### Participants

#### Recruitment

Participants are GHB dependent patients in treatment for detoxification at six participating addiction care facilities. These GHB dependent patients will be informed by their physician about the possibility to participate in the current study before GHB detoxification. The physician will inform the research nurse per centre on potential participants for the study, who will provide further study information to the patients after the detoxification. After informed consent, a research physician will perform the medical screening. The intervention group will be compared with two control groups: recently detoxified GHB dependent patients included in the Dutch national GHB Monitor 2.0, but that do not want to use baclofen (TAU only); and a matched historical control group from our previous work on GHB dependence (n = 274) of whom follow-up data are available [20]. The historical control group will be matched on age, gender, GHB use (dose and years), and number of detoxification attempts.

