#### In- and exclusion criteria

Patients are eligible to participate if GHB dependence (according to the DSM-IV general criteria of dependence) is their primary diagnosis [28] and their age is at least 18 years. All participants should be able to read and speak the Dutch language. Patients with any current somatic or psychiatric safety concerns are excluded. Exclusion criteria are liver cirrhosis and impaired renal function (as indicated by aspartate aminotransferase (AST)), alanine transaminase (ALT), or gamma-glutamyl transferase ((GGT) level >3 times the upper limit of normal (ULN); bilirubin > ULN; serum creatinine > ULN), unstable hypertension, unstable diabetes mellitus, seizure disorder including patients currently taking anticonvulsants, and pregnancy. Patients experiencing current severe mood disorder (bipolar disorder or major depressive disorder), current psychotic disorder (including schizophrenia), and/or suicidal ideations and patients suffering Parkinson’s disease will be excluded too. Co-current use of anxiolytics, stimulants or hypnotics will not be permitted.

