#### Sample size calculation

To date, there are no published studies on the effect of baclofen on relapse in GHB dependent patients. Therefore, we used the results of previous studies on the effect of baclofen in alcohol dependent patients and our previous work on GHB dependence, in order to estimate the required sample size. Two RCTs showed that baclofen was superior to placebo in increasing abstinence rates in alcohol dependent patients: 70% (14 out of 20) versus 21% (4 out of 19) within a period of 30 days [29] and 71% (30 out of 42 p) versus 29% (14 out of 42) within a period of 12 weeks [30]. These results indicate a potential increase in abstinence of 42–49% with baclofen treatment for alcohol dependence. Results of the previous national GHB project stated that 36% of the patients succeeded to avoid relapse in GHB within a period of 3 months after detoxification without any medical interventions [20]. Therefore, we will consider a percentage of importance difference in baclofen effect in the GHB dependent participants of 34% between the Baclofen + TAU group and the TAU only or the matched control group with an expected abstinence rate with baclofen of 70% as in the alcohol studies and of 36% without baclofen.

We used the following formula comparing two proportions to calculate the sample size, n = [(Zα/2 + Zβ)^2^ × {(p1 (1-p1) + (p2 (1-p2))}] / (p1 - p2)^2^, n = [(1.96+ 0.84)^2^ × {(0.7 (1–0.7) + (0.36 (1–0.36))}] / (0.34)^2^, according to [name] sample size calculator, Exeter Initiative for Statistics. The calculation estimates that the minimal total samples size of 30 patients per group would be sufficient to detect a clinical difference of 34% in two-tailed z-test of proportions (α = 0.05, β=0.80). In the alcohol studies and our previous work with GHB inpatients an attrition rate of 13–15% was reported. We anticipate a slightly higher drop-out rate of 25%, due to the outpatient component of the baclofen treatment. Therefore we will include 40 participants in the baclofen treatment group.

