The current study does have several limitations. First, the study is not randomized, nor placebo controlled. However, we will compare patients receiving baclofen with a control group matched for gender, age and the pattern of GHB use, in order to control for potential confounding factors. Second, the accompanying treatment as usual (TAU) is not identical in all participating addiction care facilities. This may confound our results. The impact of TAU will be checked with a sensitivity analysis compare patients’ results from the different centers conforming the add-on baclofen effect.

Given these methodological limitations the current study should be considered explorative in nature. Given the currently rather limited information from both preclinical and clinical studies of GHB such an explorative approach seems justified. We would also like to test the GHB substitution effect of baclofen (as a GABA-B agonist) hypothesis. It is important to evaluate of this effect is clinically recognized and obvious for the participants, and may define placebo use as non-beneficial. We need to be able to determine the margins of the required treatment dose. All forgoing justify this setup of an open label trail before a large placebo controlled randomized trial.

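### Historical controls are matched on four variables, with no statement that the trial's exclusion criteria apply to them, so selection may favour the screened baclofen group

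*Protocol article*

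**What the plan says.** The protocol article compares the baclofen group with two control groups: concurrent patients who decline baclofen, and "a matched historical control group from our previous work on GHB dependence (n = 274) of whom follow-up data are available". For the second group the Recruitment section gives the selection rule: "The historical control group will be matched on age, gender, GHB use (dose and years), and number of detoxification attempts". The only other condition is that follow-up data exist.

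Trial participants pass a further filter. Recruitment states "After informed consent, a research physician will perform the medical screening". The section on in- and exclusion criteria adds "Patients with any current somatic or psychiatric safety concerns are excluded", and lists among those excluded "Patients experiencing current severe mood disorder (bipolar disorder or major depressive disorder), current psychotic disorder (including schizophrenia), and/or suicidal ideations", together with seizure disorder, Parkinson's disease, and liver or renal values beyond set limits. These criteria are written for people entering the trial. No section extends them to the historical cohort.

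On prognosis, the abstract says "Craving for GHB use and co-morbid psychiatric symptom levels are thought to be the major factors contributing to the high relapse rates". The Background section also lists anxiety and depression after stopping GHB among patients' own reasons for relapse.

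On confounding, the limitations paragraph of the Discussion answers the lack of randomisation by pointing to a "control group matched for gender, age and the pattern of GHB use, in order to control for potential confounding factors".

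The sample size section takes its control rate from the previous national project, under the same reference number as the historical cohort: "36% of the patients succeeded to avoid relapse in GHB within a period of 3 months after detoxification without any medical interventions".

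**The concern.** One side of the historical comparison is filtered on psychiatric and medical status; the other, as written, is not. If the filtered-out patients would have relapsed more often than the rest, the baclofen group starts with a better prognosis, and the comparison can show an advantage that owes nothing to baclofen. The article gives grounds for taking this seriously, since it regards psychiatric symptoms as a main cause of relapse.

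The stated analysis does not close the gap. Under Statistical analyses, 3-month abstinence is compared with both control groups by a Pearson chi-squared test, which takes no covariates. The covariates named for all analyses are socio-demographic, with age and gender as examples. Baseline craving is used as a covariate for the craving outcome, and treatment centre enters a sensitivity analysis; neither adjusts the relapse comparison for psychiatric status.

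Two things are at stake: how far a difference from the historical group can be credited to baclofen, and whether the Discussion describes fairly what the matching controls.

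**Working it through.** **The plan's own figures.** With 70% abstinence on baclofen, 36% without, and the article's formula:

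n = (1.96 + 0.84)² × (0.70 × 0.30 + 0.36 × 0.64) / 0.34² = 29.87, rounded up to 30 per group. Allowing for 25% drop-out, 30 / 0.75 = 40. Both stated figures reproduce.

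**What the historical matching covers**

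| Factor | Baclofen group | Historical group |
|---|---|---|
| Age, gender, GHB dose and years, detoxification attempts | observed | matched |
| Severe mood disorder, psychotic disorder, suicidal ideation | excluded | not stated |
| Medical exclusions | excluded | not stated |
| Psychiatric symptom level, craving | measured at baseline | not matched |

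**How large could the effect be?** Two inputs are needed and the article gives neither, so both are assumptions:

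- f, the share of the historical cohort who would fail the trial's criteria;
- r, the 3-month abstinence rate in that share.

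If overall abstinence is 36%, the rate among patients who would pass is

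eligible rate = (0.36 − f × r) / (1 − f).

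If baclofen has no effect, the screened group abstains at this rate and an unscreened historical group at 36%. The spurious difference is the gap between them. The last column is the two-sided rejection rate at the 5% level with 30 independent patients per group and no baclofen effect (normal approximation, pooled standard error for the critical value).

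| f | r | Eligible rate | Spurious difference | Rejection rate |
|---|---|---|---|---|
| any | 36% | 36.0% | 0 points | 5% |
| 10% | 30% | 0.33 / 0.9 = 36.7% | 0.7 points | 5% |
| 20% | 20% | 0.32 / 0.8 = 40.0% | 4.0 points | 6% |
| 30% | 10% | 0.33 / 0.7 = 47.1% | 11.1 points | 14% |
| 40% | 10% | 0.32 / 0.6 = 53.3% | 17.3 points | 27% |

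The sign depends on r. If excludable patients abstained more often than 36%, the difference would run against baclofen: with f = 20% and r = 50%, the eligible rate is 0.26 / 0.8 = 32.5%, a difference of −3.5 points.

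The table takes 36% as the rate in the historical comparison group. The matched subset may have another rate, and matching on GHB use and detoxification attempts may remove part of any psychiatric imbalance that goes with them.

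**The case against.** The strongest reply is that the article never says ineligible historical patients are kept. It lists matching variables and leaves the earlier cohort to a cited source. A reader might infer that this cohort was not screened for severe mood, psychotic or medical disorders. The article does not support that: it is silent on how the cohort was selected, and the cohort may have had exclusions of its own. If those were the same as the trial's, f is zero and the problem disappears.

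A reader might also infer that screening must raise abstinence in the baclofen group, or that 36% is too low a control rate and the trial therefore underpowered. Neither follows. Several exclusions are somatic, such as liver and renal limits, unstable hypertension, pregnancy and Parkinson's disease, and the article links none of these to relapse. What it says about psychiatric factors concerns symptom levels, anxiety and depression; it does not report that patients with the excluded diagnoses relapse more. Citing only the 4 to 17 point cases would leave out the near-zero end, which is just as compatible with the text.

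Context also softens the point. There is a concurrent control group, the Discussion names non-randomisation as the first limitation and calls the study explorative, and firm conclusions are left to later randomised trials.

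All of this limits the claim without removing it. The matching rule as written includes no eligibility condition or psychiatric variable, the named covariates do not supply one, and the limitations paragraph offers the matching as its answer to confounding without mentioning the eligibility difference. A general exploratory label does not tell the reader which confounders remain open.

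**Conclusion.** The point stands in modest form. Historical controls are matched on age, gender, GHB use and number of detoxification attempts, and the article does not state that the trial's exclusion criteria apply to them. Since the article itself treats psychiatric symptoms as drivers of relapse, and neither matching nor stated covariates cover psychiatric status, the comparison may favour baclofen through selection. The Discussion overstates what the matching controls.

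Size and direction cannot be determined from the article. The illustrative range in baclofen's favour is 0 to about 17 points, against a planned difference of 34 points. It rests on assumed values of f and r, on the 36% rate holding in the matched subset, and on the earlier cohort not having been screened in a similar way. This is a cheap improvement to the design; it does not show that the historical comparison is biased.

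**What to change.** - **Recruitment.** State that, before matching, the historical pool is restricted to patients who meet the trial's in- and exclusion criteria as far as their records allow. Match on baseline psychiatric comorbidity, or adjust the relapse comparison for it, where it was recorded.
- **Sample size calculation and reporting.** Give the 3-month abstinence rate in that restricted subset beside the 36%.
- **Discussion, limitations.** State which criteria could not be applied to the historical records and that matching does not control for them. Describe the historical comparison as supportive of the concurrent comparison.
- **Concurrent group.** Confirm that the same criteria apply there. The Study design section makes assignment depend on the criteria as well as on preference, while Recruitment describes this group only as patients who do not want baclofen.

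The cost is a filter on existing records and some wording. Fewer historical patients remain for matching: if all 274 have follow-up and 40% were removed, 274 × 0.6 gives about 164, or roughly 4 candidates for each of the 40 baclofen patients. The apparent difference may shrink. How much can be done depends on what was recorded; the article does not say whether diagnoses or laboratory values are available, and it reports that adjunct psychological treatment in this group is not. Where a criterion was not recorded, only the limitation statement is possible.

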#### In- and exclusion criteria

Patients are eligible to participate if GHB dependence (according to the DSM-IV general criteria of dependence) is their primary diagnosis [28] and their age is at least 18 years. All participants should be able to read and speak the Dutch language. Patients with any current somatic or psychiatric safety concerns are excluded. Exclusion criteria are liver cirrhosis and impaired renal function (as indicated by aspartate aminotransferase (AST)), alanine transaminase (ALT), or gamma-glutamyl transferase ((GGT) level >3 times the upper limit of normal (ULN); bilirubin > ULN; serum creatinine > ULN), unstable hypertension, unstable diabetes mellitus, seizure disorder including patients currently taking anticonvulsants, and pregnancy. Patients experiencing current severe mood disorder (bipolar disorder or major depressive disorder), current psychotic disorder (including schizophrenia), and/or suicidal ideations and patients suffering Parkinson’s disease will be excluded too. Co-current use of anxiolytics, stimulants or hypnotics will not be permitted.

#### Sample size calculation

To date, there are no published studies on the effect of baclofen on relapse in GHB dependent patients. Therefore, we used the results of previous studies on the effect of baclofen in alcohol dependent patients and our previous work on GHB dependence, in order to estimate the required sample size. Two RCTs showed that baclofen was superior to placebo in increasing abstinence rates in alcohol dependent patients: 70% (14 out of 20) versus 21% (4 out of 19) within a period of 30 days [29] and 71% (30 out of 42 p) versus 29% (14 out of 42) within a period of 12 weeks [30]. These results indicate a potential increase in abstinence of 42–49% with baclofen treatment for alcohol dependence. Results of the previous national GHB project stated that 36% of the patients succeeded to avoid relapse in GHB within a period of 3 months after detoxification without any medical interventions [20]. Therefore, we will consider a percentage of importance difference in baclofen effect in the GHB dependent participants of 34% between the Baclofen + TAU group and the TAU only or the matched control group with an expected abstinence rate with baclofen of 70% as in the alcohol studies and of 36% without baclofen.

We used the following formula comparing two proportions to calculate the sample size, n = [(Zα/2 + Zβ)^2^ × {(p1 (1-p1) + (p2 (1-p2))}] / (p1 - p2)^2^, n = [(1.96+ 0.84)^2^ × {(0.7 (1–0.7) + (0.36 (1–0.36))}] / (0.34)^2^, according to [name] sample size calculator, Exeter Initiative for Statistics. The calculation estimates that the minimal total samples size of 30 patients per group would be sufficient to detect a clinical difference of 34% in two-tailed z-test of proportions (α = 0.05, β=0.80). In the alcohol studies and our previous work with GHB inpatients an attrition rate of 13–15% was reported. We anticipate a slightly higher drop-out rate of 25%, due to the outpatient component of the baclofen treatment. Therefore we will include 40 participants in the baclofen treatment group.

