### Statistical analyses

Descriptive analysis will be executed for all measurements and will include the mean, SD and frequencies of events with confidence intervals. Descriptive statistics will be used to compare the basic characteristics of the participants in the experimental group and the control groups. To assess any difference in relapse rates between the experimental group and the control groups (TAU group and matched historical group) at 3 month after detoxification Pearson Chi-squared test will be used for the dichotomous abstinence rates. ANOVA will be carried out on continuous variables, such as the total number of abstinent days, the maximum duration of continued abstinence, time before relapse (relapse defined as ≥ 3 times GHB use per day, for 2 subsequent days), and level of substance use over a period of 3 months. At 6 months period participants who continued baclofen will be compared to those who have stopped with baclofen (after 3 month) on relapse into GHB abuse or abstinence corrected for craving. The numbers of patients maintaining abstinence will be analysed with the intention-to-treat principles. The difference in craving will be analysed by MANCOVA at 3 months between groups (abstinent experimental versus abstinent TAU or relapsed TAU) with DDQ and VAS craving as dependent variables and corrected for craving levels immediately after detoxification. The change in craving in time during the baclofen treatment will be analysed via repeated measures MANOVA. By means of MANCOVA at 6 months after detoxification the difference in craving among participants who are still using baclofen and those who have discontinued baclofen will be analysed corrected for craving after 3 months. The effect of baclofen on the psychiatric symptoms levels (DASS, MINI) and also quality of life (EQ–5D) will be analyzed similarly as for craving at 3 and 6 months. The effects of the different TAU approaches as potential confounders will be tested in a sensitivity analyses (changing one-factor-at-a-time) in an linear regression including TAU per center as covariates.

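### The sample-size statement gives β as 0.80 where its own formula uses β = 0.20, and 30 evaluable patients per group give about 77% exact power, not the 80% intended

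*Protocol article*

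**What the plan says.** All sizing statements are in the protocol article, under Sample size calculation. The design assumes "an expected abstinence rate with baclofen of 70% as in the alcohol studies and of 36% without baclofen", an absolute difference of 34 points. The section prints a two-proportion formula with the unpooled variance, Zα/2 = 1.96 and Zβ = 0.84. It concludes that 30 per group are "sufficient to detect a clinical difference of 34% in two-tailed z-test of proportions (α = 0.05, β=0.80"). It then allows for 25% drop-out and plans 40 patients in the baclofen group.

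Under Statistical analyses, the comparison of relapse between groups at 3 months is assigned to a named test: "Pearson Chi-squared test will be used for the dichotomous abstinence rates".

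The same sizing section cites two alcohol trials as background. One is reported as "71% (30 out of 42 p) versus 29% (14 out of 42) within a period of 12 weeks", and the two together are summarised as "a potential increase in abstinence of 42–49" percent.

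**The concern.** Two statements about the design's error rates do not stand as printed.

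First, "α = 0.05, β=0.80" gives the type II error the value that belongs to power. A reader who takes the symbol at its definition gets a trial with a 20% chance of detecting its target difference, while the formula in the same paragraph uses the quantile for 80%.

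Second, once the label is corrected, the paragraph implies 80% power at 30 per group. That comes from a large-sample formula. With 30 patients per group and binary data it is worth checking whether the test delivers it, because this paragraph is the whole justification of the trial's size, and a non-significant result would be read against the stated power.

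A smaller matter is that one of the cited counts disagrees with the percentage printed beside it, and the summary range is built on that percentage.

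**Working it through.** **Inputs** (all from Sample size calculation): p1 = 0.70, p2 = 0.36, difference 0.34, two-sided α = 0.05, Zα/2 = 1.96, Zβ = 0.84, 30 evaluable per group, 25% drop-out. The test is from Statistical analyses: Pearson chi-squared, taken here without continuity correction.

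**1. The plan's own figure.**
- Variance term: 0.70 × 0.30 + 0.36 × 0.64 = 0.2100 + 0.2304 = 0.4404.
- n = (1.96 + 0.84)² × 0.4404 / 0.34² = 7.84 × 0.4404 / 0.1156 = 29.87, so 30 per group.
- Drop-out: 30 / (1 − 0.25) = 40.

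Both figures reproduce.

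**2. The β label.** Zβ = 0.84 is the standard normal quantile for 80% power, that is β = 0.20. With β really equal to 0.80 the quantile would be −0.84, and the same formula would give (1.96 − 0.84)² × 0.4404 / 0.1156 = 4.8, about 5 per group. The 30 was therefore calculated with β = 0.20.

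**3. Power that the formula implies at 30.** The standard error is √(0.4404 / 30) = 0.1212. Then 0.34 / 0.1212 − 1.96 = 0.846, and Φ(0.846) = 80.1%.

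**4. Exact power.** Every pair of abstinence counts in the two groups was enumerated with its binomial probability under 70% and 36%. The probabilities of the pairs at which the test rejects (|z| > 1.96) were then summed.

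| n per group | Pearson chi-squared (pooled) | Unpooled z-test |
|---|---|---|
| 30 | 77.3% | 77.4% |
| 31 | 79.6% | 79.7% |
| 32 | 81.7% | 81.7% |
| 33 | 83.6% | 83.6% |
| 40 | 88.7% | 88.7% |

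At 30 per group the shortfall from 80% is 2.7 points for the Pearson test, and almost the same for the unpooled test. Pearson power first reaches 80% at 32. Exact power does not rise smoothly (Pearson falls to 80.5% at 34), because the counts are discrete.

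**5. Unequal groups.** Exact Pearson power is 82.4% at 30 versus 40 and 87.3% at 30 versus 60.

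**6. The alcohol benchmark.** 30/42 = 71.4%. 14/42 = 33.3%, whereas 29% would correspond to 12/42 = 28.6%. From the printed percentages the difference is 71 − 29 = 42 points; from the printed counts it is (30 − 14)/42 = 38 points. The other trial gives 70 − 21 = 49 points. The sizing formula uses 70%, 36% and 34 points, so neither the 29% nor the 42–49 range enters it.

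**The case against.** The strongest reply is that nothing here is an arithmetic error in the sample size. The printed formula is a standard variant and gives 30. The β label is resolved by the Zβ in the same paragraph. A gap of under 3 points is small beside the uncertainty in rates partly borrowed from alcohol trials: raising the assumed baclofen rate from 70% to 71% moves exact power at 30 per group to 79.8%. The protocol's Discussion also calls the study explorative. All of this stands. It keeps the point small, but the printed β is still wrong and the implied 80% is still not delivered at the stated rates.

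A second reply is that the analysis will not rest on two groups of exactly 30. The Recruitment section describes a pool of 274 historical patients for matching and states no matching ratio, so that comparison may have more power. Abstinence is to be analysed by intention to treat, and with all 40 per group at unchanged rates exact power is 88.7%. This stands in part. The section makes its claim about 30 per group, and that is the claim to correct. Nor is 88.7% assured: if, as an assumption, 25% of each group drop out and count as relapsed, the rates become 0.75 × 70% = 52.5% and 0.75 × 36% = 27%, and exact Pearson power at 40 per group is about 66%.

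A reader might also infer that the shortfall arises because the formula is unpooled while the Pearson test pools the variance. The pooled normal approximation does give a lower figure at 30 (76.5%, against 80.1% unpooled), which makes this tempting. The exact results do not support it: at 30 per group an unpooled z-test has the same power to within 0.1 point. The cause is the optimism of the unpooled approximation at small n, not a conflict between the two sections.

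**Conclusion.** The point holds, at modest size. The printed β of 0.80 contradicts the paragraph's own Zβ and should be 0.20. It does not mean that the trial was sized for 20% power; the figure of 30 rules that out. Separately, 30 evaluable patients in each of two equal groups give about 77% exact power rather than 80%, with 80% first reached at 32. The label slip plays no part in this 77%.

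The power figure assumes true abstinence of 70% and 36%, equal groups of 30, two-sided α = 0.05 and no continuity correction. A larger historical comparison group would raise it.

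The mismatch between 14 of 42 and 29% is real but has no effect on the sizing. A reader might conclude that the alcohol trial's difference is 38 points and not 42. The document cannot settle that: the percentages agree with the printed 42, and either the count or the percentage may be the misprint.

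**What to change.** In Sample size calculation:

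- State the error rates as α = 0.05 two-sided and β = 0.20 (nominal power 80%).
- Say that 30 per group comes from a normal-approximation formula, and that 30 evaluable patients in each of two equal groups give about 77% exact power for the Pearson chi-squared test at 70% versus 36%. Add that power is higher if the matched historical group is larger, for example 87% at 30 versus 60.
- Check the cited alcohol trial and reconcile 14 of 42 with 29%. Change the range to 38–49% only if the count proves right; if the percentage is right, correct the count and leave the range.

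The cost is a few edited sentences and a slightly less favourable power statement. Enrolment, the planned test and the analysis stay as they are.
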